#### Descriptive analyses

The flow of participants through each stage of the trial, including the number of individuals screened, randomised, receiving treatment as allocated, and included in the primary analysis, will be summarised using a CONSORT flow chart [19] (Fig. 1).

**Fig. 1 Fig1:**
[figure not shown]
CONSORT flow diagram for participants in trial up to final assessment

The baseline comparability of the two randomised groups in terms of minimisation factors, demographic characteristics, and clinical genetics will be presented (Table 3).

**Table 3 Tab3:** Baseline characteristics and clinical genetics

	6 months surgery	12 months surgery	Overall
Number of patients	XX	XX	XX
Baseline characteristics			
Gender			
*N*	XX	XX	XX
Male*; n (%)*	XX (XX.X)	XX (XX.X)	XX (XX.X)
Female*; n (%)*	XX (XX.X)	XX (XX.X)	XX (XX.X)
*Not known; n*	XX	XX	XX
Gestational age (weeks)			
*N*	XX	XX	XX
*Mean (SD)*	XX.X (XX.X)	XX.X (XX.X)	XX.X (XX.X)
*Median (IQR)*	XX.X (XX.X)	XX.X (XX.X)	XX.X (XX.X)
*(Min, max)*	(XX.X, XX.X)	(XX.X, XX.X)	(XX.X, XX.X)
*Not known; n*	XX	XX	XX
Size of cleft			
*N*	XX	XX	XX
*Soft palate only; n (%)*	XX (XX.X)	XX (XX.X)	XX (XX.X)
*Soft and hard palate; n (%)*	XX (XX.X)	XX (XX.X)	XX (XX.X)
*Not known; n*	XX	XX	XX
Clinical genetics			
Ethnicity			
*White; n (%)*	XX (XX.X)	XX (XX.X)	XX (XX.X)
*Black; n (%)*	XX (XX.X)	XX (XX.X)	XX (XX.X)
*Asian; n (%)*	XX (XX.X)	XX (XX.X)	XX (XX.X)
*Chinese; n (%)*	XX (XX.X)	XX (XX.X)	XX (XX.X)
*Mixed; n (%)*	XX (XX.X)	XX (XX.X)	XX (XX.X)
*Other; n (%)*	XX (XX.X)	XX (XX.X)	XX (XX.X)
*Not stated; n (%)*	XX (XX.X)	XX (XX.X)	XX (XX.X)
*Not known; n*	XX	XX	XX
Weight at examination (grammes)			
*N*	XX	XX	XX
*Mean (SD)*	XX.X (XX.X)	XX.X (XX.X)	XX.X (XX.X)
*Median (IQR)*	XX.X (XX.X)	XX.X (XX.X)	XX.X (XX.X)
*(Min, max)*	(XX.X, XX.X)	(XX.X, XX.X)	(XX.X, XX.X)
*Not known; n*	XX	XX	XX
Length at examination (cm)			
*N*	XX	XX	XX
*Mean (SD)*	XX.X (XX.X)	XX.X (XX.X)	XX.X (XX.X)
*Median (IQR)*	XX.X (XX.X)	XX.X (XX.X)	XX.X (XX.X)
*(Min, max)*	(XX.X, XX.X)	(XX.X, XX.X)	(XX.X, XX.X)
*Not known; n*	XX	XX	XX
Occipitofrontal circumference (cm)			
*N*	XX	XX	XX
*Mean (SD)*	XX.X (XX.X)	XX.X (XX.X)	XX.X (XX.X)
*Median (IQR)*	XX.X (XX.X)	XX.X (XX.X)	XX.X (XX.X)
*(Min, max)*	(XX.X, XX.X)	(XX.X, XX.X)	(XX.X, XX.X)
*Not known; n*	XX	XX	XX
Interpretation of DENVER-II			
*Normal; n (%)*	XX (XX.X)	XX (XX.X)	XX (XX.X)
*Suspect; n (%)*	XX (XX.X)	XX (XX.X)	XX (XX.X)
*Un-testable; n (%)*	XX (XX.X)	XX (XX.X)	XX (XX.X)
*Not known; n*	XX	XX	XX
Diagnosis			
*Known syndrome; n (%)*	XX (XX.X)	XX (XX.X)	XX (XX.X)
*Unknown syndrome; n (%)*	XX (XX.X)	XX (XX.X)	XX (XX.X)
*Severe developmental delay; n (%)*	XX (XX.X)	XX (XX.X)	XX (XX.X)
*Uncertain; n (%)*	XX (XX.X)	XX (XX.X)	XX (XX.X)
*Non-syndromic; n (%)*	XX (XX.X)	XX (XX.X)	XX (XX.X)
*Not known; n*	XX	XX	XX

The surgical comparability of the two randomised groups in terms of baseline surgery characteristics, intra-operative events, early complications during the hospital stay, observations monitored 48 h post-surgery, and postoperative medication will be presented (Table 4).

**Table 4 Tab4:** Surgery characteristics and observations

	6 months surgery	12 months surgery	Overall
Number of patients	XX	XX	XX
Baseline surgery characteristics			
Grading of cleft at surgery			
*N*	XX	XX	XX
*Grade1; n (%)*	XX (XX.X)	XX (XX.X)	XX (XX.X)
*Grade 2; n (%)*	XX (XX.X)	XX (XX.X)	XX (XX.X)
*Grade 3; n (%)*	XX (XX.X)	XX (XX.X)	XX (XX.X)
*Grade 4; n (%)*	XX (XX.X)	XX (XX.X)	XX (XX.X)
*Not known; n*	XX	XX	XX
Shape of cleft			
*N*	XX	XX	XX
*“U” shaped; n (%)*	XX (XX.X)	XX (XX.X)	XX (XX.X)
*“V” shaped; n (%)*	XX (XX.X)	XX (XX.X)	XX (XX.X)
*Not known; n*	XX	XX	XX
Dimensions of cleft palate (mm)			
Soft tissue width at posterior hard plate			
*N*	XX	XX	XX
*Mean (SD)*	XX.X (XX.X)	XX.X (XX.X)	XX.X (XX.X)
*Median (IQR)*	XX.X (XX.X)	XX.X (XX.X)	XX.X (XX.X)
*(Min, max)*	(XX.X, XX.X)	(XX.X, XX.X)	(XX.X, XX.X)
*Not known; n*	XX	XX	XX
Bony width at posterior hard palate			
*N*	XX	XX	XX
*Mean (SD)*	XX.X (XX.X)	XX.X (XX.X)	XX.X (XX.X)
*Median (IQR)*	XX.X (XX.X)	XX.X (XX.X)	XX.X (XX.X)
*(Min, max)*	(XX.X, XX.X)	(XX.X, XX.X)	(XX.X, XX.X)
*Not known; n*	XX	XX	XX
Width at base of uvula			
*N*	XX	XX	XX
*Mean (SD)*	XX.X (XX.X)	XX.X (XX.X)	XX.X (XX.X)
*Median (IQR)*	XX.X (XX.X)	XX.X (XX.X)	XX.X (XX.X)
*(Min, max)*	(XX.X, XX.X)	(XX.X, XX.X)	(XX.X, XX.X)
*Not known; n*	XX	XX	XX
Length of soft palate (distal base of uvula-hard palate)			
*N*	XX	XX	XX
*Mean (SD)*	XX.X (XX.X)	XX.X (XX.X)	XX.X (XX.X)
*Median (IQR)*	XX.X (XX.X)	XX.X (XX.X)	XX.X (XX.X)
*(Min, max)*	(XX.X, XX.X)	(XX.X, XX.X)	(XX.X, XX.X)
*Not known; n*	XX	XX	XX
Intra-operative events			
Blood transfusion during surgery			
*N*	XX	XX	XX
*Yes; n (%)*	XX (XX.X)	XX (XX.X)	XX (XX.X)
*No; n (%)*	XX (XX.X)	XX (XX.X)	XX (XX.X)
*Not known; n*	XX	XX	XX
Anaesthetic complications			
*N*	XX	XX	XX
*Yes; n (%)*	XX (XX.X)	XX (XX.X)	XX (XX.X)
*No; n (%)*	XX (XX.X)	XX (XX.X)	XX (XX.X)
*Not known; n*	XX	XX	XX
Bleeding			
*N*	XX	XX	XX
*Yes; n (%)*	XX (XX.X)	XX (XX.X)	XX (XX.X)
*No; n (%)*	XX (XX.X)	XX (XX.X)	XX (XX.X)
*Not known; n*	XX	XX	XX
Early complications during the hospital stay			
Postoperative airway problems			
*N*	XX	XX	XX
*Yes; n (%)*	XX (XX.X)	XX (XX.X)	XX (XX.X)
*No; n (%)*	XX (XX.X)	XX (XX.X)	XX (XX.X)
*Not known; n*	XX	XX	XX
Postoperative blood loss			
*N*	XX	XX	XX
*Yes; n (%)*	XX (XX.X)	XX (XX.X)	XX (XX.X)
*No; n (%)*	XX (XX.X)	XX (XX.X)	XX (XX.X)
*Not known; n*	XX	XX	XX
Anti-coagulants given			
*N*	XX	XX	XX
*Yes; n (%)*	XX (XX.X)	XX (XX.X)	XX (XX.X)
*No; n (%)*	XX (XX.X)	XX (XX.X)	XX (XX.X)
*Not known; n*	XX	XX	XX
Dehiscence			
*N*	XX	XX	XX
*Yes; n (%)*	XX (XX.X)	XX (XX.X)	XX (XX.X)
*No; n (%)*	XX (XX.X)	XX (XX.X)	XX (XX.X)
*Not known; n*	XX	XX	XX
Readmission to operating room			
*N*	XX	XX	XX
*Yes; n (%)*	XX (XX.X)	XX (XX.X)	XX (XX.X)
*No; n (%)*	XX (XX.X)	XX (XX.X)	XX (XX.X)
*Not known; n*	XX	XX	XX
Observations monitored in first 48 h post-surgery			
Oxygen saturation levels			
*N*	XX	XX	XX
*Clinically significant abnormality; n (%)*	XX (XX.X)	XX (XX.X)	XX (XX.X)
*No clinically significant abnormality; n (%)*	XX (XX.X)	XX (XX.X)	XX (XX.X)
*No observation; n (%)*	XX (XX.X)	XX (XX.X)	XX (XX.X)
*Not known; n*	XX	XX	XX
Carbon dioxide and oxygen			
*N*	XX	XX	XX
*Clinically significant abnormality; n (%)*	XX (XX.X)	XX (XX.X)	XX (XX.X)
*No clinically significant abnormality; n (%)*	XX (XX.X)	XX (XX.X)	XX (XX.X)
*No observation; n (%)*	XX (XX.X)	XX (XX.X)	XX (XX.X)
*Not known; n*	XX	XX	XX
Arterial blood gases			
*N*	XX	XX	XX
*Clinically significant abnormality; n (%)*	XX (XX.X)	XX (XX.X)	XX (XX.X)
*No clinically significant abnormality; n (%)*	XX (XX.X)	XX (XX.X)	XX (XX.X)
*No observation; n (%)*	XX (XX.X)	XX (XX.X)	XX (XX.X)
*Not known; n*	XX	XX	XX
Heart rate			
*N*	XX	XX	XX
*Clinically significant abnormality and treatment required; n (%)*	XX (XX.X)	XX (XX.X)	XX (XX.X)
*Clinically significant abnormality and no treatment required; n (%)*	XX (XX.X)	XX (XX.X)	XX (XX.X)
*No clinically significant abnormality; n (%)*	XX (XX.X)	XX (XX.X)	XX (XX.X)
*No observation; n (%)*	XX (XX.X)	XX (XX.X)	XX (XX.X)
*Not known; n*	XX	XX	XX
Blood pressure			
*N*	XX	XX	XX
*Clinically significant abnormality and treatment required; n (%)*	XX (XX.X)	XX (XX.X)	XX (XX.X)
*Clinically significant abnormality and no treatment required; n (%)*	XX (XX.X)	XX (XX.X)	XX (XX.X)
*No clinically significant abnormality; n (%)*	XX (XX.X)	XX (XX.X)	XX (XX.X)
*No observation; n (%)*	XX (XX.X)	XX (XX.X)	XX (XX.X)
*Not known; n*	XX	XX	XX
Respiration			
*N*	XX	XX	XX
*Clinically significant abnormality; n (%)*	XX (XX.X)	XX (XX.X)	XX (XX.X)
*No clinically significant abnormality; n (%)*	XX (XX.X)	XX (XX.X)	XX (XX.X)
*No observation; n (%)*	XX (XX.X)	XX (XX.X)	XX (XX.X)
*Not known; n*	XX	XX	XX
Body temperature			
*N*	XX	XX	XX
*Clinically significant abnormality and treatment required; n (%)*	XX (XX.X)	XX (XX.X)	XX (XX.X)
*Clinically significant abnormality and no treatment required; n (%)*	XX (XX.X)	XX (XX.X)	XX (XX.X)
*No clinically significant abnormality; n (%)*	XX (XX.X)	XX (XX.X)	XX (XX.X)
*No observation; n (%)*	XX (XX.X)	XX (XX.X)	XX (XX.X)
*Not known; n*	XX	XX	XX
Postoperative medication			
Pain relief medication			
*N*	XX	XX	XX
*Yes; n (%)*	XX (XX.X)	XX (XX.X)	XX (XX.X)
*No; n (%)*	XX (XX.X)	XX (XX.X)	XX (XX.X)
*Not known; n*	XX	XX	XX
Anti-inflammatory medication			
*N*	XX	XX	XX
*Yes; n (%)*	XX (XX.X)	XX (XX.X)	XX (XX.X)
*No; n (%)*	XX (XX.X)	XX (XX.X)	XX (XX.X)
*Not known; n*	XX	XX	XX
Antibiotic medication (other than prophylactic antibiotics)			
*N*	XX	XX	XX
*Yes; n (%)*	XX (XX.X)	XX (XX.X)	XX (XX.X)
*No; n (%)*	XX (XX.X)	XX (XX.X)	XX (XX.X)
*Not known; n*	XX	XX	XX

Binary and categorical data will be summarised by frequencies and percentages. Continuous data will be presented by means and standard deviations (SDs), or medians and inter-quartile range (IQR) if data are skewed. Tests of statistical significance will not be undertaken for baseline characteristics; rather, the clinical importance of any imbalance will be noted. The amount missing in each case will be summarised.

#### Lost to follow-up, withdrawals, and missing data

The timing of withdrawal in relation to surgery and scheduled visits, level of withdrawal, who made the decision, and reason for withdrawal will be summarised both overall and for each randomised group. Frequencies will be presented along with percentages using the number of participants who withdrew as the denominator.

The number lost to follow-up both overall and within each randomised group will be reported, and the reasons where known will be documented. Any deaths and their causes will be reported separately.

Based on experience from the ScandCleft study, the structure of the centralised cleft palate care system and trial-specific systems in place will ensure the occurrence of missing data is likely to be low. Therefore, the potential impact of any missing data is likely to be low. For all assessments and outcomes, participants with insufficient data to make their assessments will be expressed as a frequency and a percentage with the denominator being those who were randomised, treated, and consented.

#### Adherence

Reasons for participants not receiving the randomised allocation will be summarised in a table. Adherence with follow-up time points (30 days, 12 months, 3 and 5 years) will be summarised at the visit level (at least one scheduled assessment visit completed per time point) and assessment level, which will specify adherence to specific assessments. When applicable, whether or not assessments were made within the expected window (Table 5) will be presented. Summaries will be presented both overall and for each randomised group.

**Table 5 Tab5:** Follow-up visits: estimated visit dates and corresponding window limits

Time point	Estimated visit date, calculated from date of birth	Window limits of estimated visit date	
		Earliest	Latest
12 months	52 weeks^1^	*6 months arm:* − 4 weeks	+ 48 weeks (equivalent to 23 months of age)^2^
		*12 months arm:* − 2 weeks	
3 years	156 weeks	− 4 weeks	+ 48 weeks (equivalent to 3 years 11 months of age)
5 years	260 weeks	− 4 weeks	+ 48 weeks (equivalent to 5 years 11 months of age)

^1^Corrected for gestational age. Full term is defined as day 1 of the 40th week of pregnancy

^2^Speech assessments vary in their latest acceptable date:

• Six months surgery patients should have their speech assessed by + 26 weeks (equivalent to 18 months of age)

• Twelve months surgery should have their speech assessed before surgery

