##### Dichotomous outcomes

For outcomes of this type, see Table 6, the number of participants categorised as having, or not having, the outcome of interest will be summarised overall, for each randomised group by frequencies and percentages. The numbers with the outcome between the randomised groups will be compared using a chi-squared test, with the relative risk [20] and 95% CI also reported.

In the circumstance that the expected number of participants with and without the outcome for each randomised group contains less than five participants, thereby raising concerns over the appropriateness of a chi-squared test, then Fisher’s exact test will be used.

No sensitivity analysis will be performed.

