##### Long ordinal, bounded continuous, and continuous outcomes

Outcomes of this type, see Table 6, will be summarised overall and for each randomised group by means and SDs, or medians and IQRs if data are skewed. Minimum and maximum values will also be presented.

Means will be compared between the two randomised groups using a *t* test or by using a non-parametric equivalent. Testing for normality of data distributions will be based using a QQ plot by randomised group. Ninety-five percent confidence intervals will be presented around the effect measure.

No sensitivity analysis will be performed.

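### 12-month speech outcomes 3a–3c may be assessed much later in the 6-month arm than in the 12-month arm, but are compared without age adjustment or any sensitivity analysis

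*SAP article*

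**What the plan says.** Table 5 (section Adherence) gives both arms the same 12-month target of 52 weeks, with the footnote "Corrected for gestational age. Full term is defined as day 1 of the 40th week of pregnancy". The limits around that target differ by arm. The earliest date is 4 weeks before target in the 6-month arm and 2 weeks before in the 12-month arm. The general latest date is common to both: "48 weeks (equivalent to 23 months of age"). Footnote 2 then sets separate latest dates for speech: "Six months surgery patients should have their speech assessed by + 26 weeks (equivalent to 18 months of age") and "Twelve months surgery should have their speech assessed before surgery".

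The analysis sections take no account of this. For dichotomous outcomes, including 3a, "The numbers with the outcome between the randomised groups will be compared using a chi-squared test", with a relative risk. Outcomes 3b and 3c get a t test or a non-parametric equivalent. Both sections state "No sensitivity analysis will be performed". Age at assessment is not a covariate in any planned analysis. Under Adherence, the plan will only tabulate, overall and by arm, whether assessments fell inside the window. The one window-based exclusion is in the sensitivity analysis of the 5-year primary outcome.

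**The concern.** A child assessed at 17 months can be expected to babble more, and to use more consonants, than one assessed at 12 months, whenever the palate was repaired. That expectation is an assumption here; the article gives no age slope. The schedule leaves room for late speech visits up to 18 months in the 6-month arm, and closes the window at surgery in the 12-month arm. Any resulting age difference arises after allocation, so randomisation does not protect against it. Blinded rating of the recordings does not remove it either.

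If the 6-month arm is older on average, a 12-month speech benefit could appear with no effect of surgical timing, and in the direction the trial is designed to detect. Each of 3a–3c is read at p ≤ 0.05 without multiplicity adjustment, so a modest shift could be reported as a finding.

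**Working it through.** **1. Table 5's own equivalences.** One month is 365.25/(12 × 7) = 4.348 weeks. Latest speech date in the 6-month arm: 52 + 26 = 78 weeks, and 78/4.348 = 17.9 months (stated: 18). General latest date: 52 + 48 = 100 weeks, and 100/4.348 = 23.0 months (stated: 23). Both are reproduced.

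**2. Permitted windows, in weeks of corrected age.**

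| 12-month assessments | 6-month arm | 12-month arm |
|---|---|---|
| Speech (3a–3c) | 48 to 78, midpoint 63 | 50 to date of surgery |
| Hearing, tympanometry, growth | 48 to 100, midpoint 74 | 50 to 100, midpoint 75 |

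The article gives no latest age for surgery in the 12-month arm, so the end of its speech window has to be assumed:

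| Assumed surgery (weeks) | Window width | Midpoint | 63 minus midpoint |
|---|---|---|---|
| 52 | 2 | 51 | 12 |
| 54 | 4 | 52 | 11 |
| 56 | 6 | 53 | 10 |
| 60 | 10 | 55 | 8 |

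These midpoints describe what is allowed, not when children were seen. For the non-speech outcomes the midpoints differ by 1 week, with the 6-month arm the younger.

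**3. Effect of a mean age gap on type I error.** Inputs: 558 recruited (Trial status), 558/2 = 279 per arm, less the 10% attrition in Sample size, giving 279 × 0.9 ≈ 251. Assume no true effect, a two-sided 5% test, and an outcome that rises linearly with age.

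- Standard error of a standardised difference: SE = √(2/251) = 0.0893.
- Shift: d = gap in weeks × slope in SD per week.
- Rejection rate: Φ(d/SE − 1.96) + Φ(−d/SE − 1.96).
- Example, 4 weeks at 0.02 SD per week: d = 0.08, d/SE = 0.896, and Φ(−1.064) + Φ(−2.856) = 0.144 + 0.002 = 14.6%.

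| Mean gap | 0.01 SD/week | 0.02 SD/week | 0.04 SD/week |
|---|---|---|---|
| 0 weeks | 5.0% | 5.0% | 5.0% |
| 2 weeks | 5.6% | 7.3% | 14.6% |
| 4 weeks | 7.3% | 14.6% | 43.4% |

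With all 279 per arm, the 4-week row is 7.6%, 15.7% and 47.2%. For the dichotomous 3a, a 50% base rate rising by 0.5 to 2 percentage points per week gives 5.6% to 14.6% at 2 weeks and 7.3% to 43.6% at 4 weeks.

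**4. What such a gap requires.** Suppose everyone else is seen on target, and some of the 6-month arm are seen 12 weeks late, at 64 weeks and well inside the window. One sixth of the arm late gives a mean gap of 12/6 = 2 weeks. One third late gives 12/3 = 4 weeks.

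**5. Whether the planned tables would reveal it.** A 6-month-arm child seen at 17 months (74 weeks) and a 12-month-arm child seen just before surgery at 12 months both count as in window. Complete adherence in both arms is therefore compatible with a material difference in mean age.

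**The case against.** The strongest reply is that Table 5 sets permitted limits around one shared target. If visits cluster near 52 weeks in both arms, the bias is close to nil. That stands: the article gives neither observed ages nor slopes, so step 3 shows sensitivity and is not an estimate.

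A reader might infer more in four respects, and the document does not support it.

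- **That all 12-month outcomes are affected.** Hearing, tympanometry and growth have the same latest limit in both arms. The only difference is 2 weeks at the early end, which lets the 6-month arm be younger. Some 12-month-arm children may have these measured before surgery and others after, but that is a separate question from age bias.
- **That late speech visits are impossible in the 12-month arm.** Its limit is the surgery date, not an age. If surgery is delayed, speech assessment can be late too; at an assumed 78 weeks the midpoint difference in step 2 would be 63 − 64 = −1 week.
- **That the window allows an arm-level gap of several months.** The 78-week limit is an individual maximum. Step 4 shows that even a 4-week mean gap needs a sizeable share of late visits.
- **That an age-adjusted model should become the main comparison.** Age at assessment is measured after randomisation, and the arms may overlap little in age, so adjustment would partly extrapolate. A supportive role is proportionate.

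These are also secondary outcomes. The 5-year primary outcome has one window for both arms and a window-based sensitivity analysis, so it is untouched.

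**Conclusion.** The point holds for 3a, 3b and 3c only. The plan allows speech assessment in different corrected-age ranges by arm, compares the arms without regard to age, rules out any check, and proposes adherence reporting that could not expose the problem. The consequence is a conditional risk: it needs outcomes that rise with age and a 6-month arm assessed later on average. Under the assumed slopes of 0.01 to 0.04 SD per week and 251 per arm, the false-positive rate runs from 5% with no gap, through about 6% to 15% at 2 weeks, to about 7% to 43% at 4 weeks. The document does not show that 12-month babbling differences do reflect age, and gives no ground for extending the point to hearing, tympanometry or growth. The trial's main conclusion is not in question, but the early speech results could be misread.

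**What to change.** For outcomes 3a–3c:

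1. Remove the statement that no sensitivity analysis will be done.
2. Report corrected age at speech assessment by arm (mean, SD, median, range), alongside the in-window counts.
3. Keep the planned test as the main comparison and prespecify two supportive analyses: (i) regression of the outcome on randomised group and corrected age at assessment, logistic for 3a and linear for 3b and 3c; (ii) the same comparison restricted to the corrected-age range in which both arms were assessed.
4. State that a 12-month speech difference will be interpreted in the light of both.

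The cost is a few lines in the SAP and short code. Assessment dates are already needed for the window summary. Recruitment closed in July 2015 and analysis follows the last visit in July 2020, so the windows cannot be changed but the analysis can still be fixed in advance. The downsides are that the restricted set drops late 6-month-arm visits and loses some precision, and that the adjusted model is reliable only where the two arms overlap in age.

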#### Analysis of primary outcome

The number of participants at age 5 years who have the primary outcome of insufficient velopharyngeal function (VPC sum ≥ 4) or not (VPC sum < 4) will be summarised overall, for each randomised group and for each region (defined according to the location of the recruiting site: Brazil, Scandinavia, UK) by frequencies and percentages. The numbers of insufficient velopharyngeal function or not between the randomised groups will be compared using a chi-squared test, with the relative risk [20] and 95% confidence interval (95% CI) also reported.

In the circumstance that the expected insufficient VPC sum or not for each randomised group contains less than five participants, thereby raising concerns over the appropriateness of a chi-squared test, then Fisher’s exact test will be used.

For inclusion in the primary analysis set, a participant must have an eligible 5-year speech recording for SLT assessment. An eligible speech recording requires the child to have attempted at least 18 of the 36 pre-specified target words for assessment of non-oral and VPI symptom and 5 of the 9 pre-specified words for hypernasality. Participants who have speech recordings that do not meet the inclusion criteria, have a recording that could not be assessed (e.g. insufficient sound), or did not complete a speech recording will be excluded from the analysis.

A sensitivity analysis will be performed to check the robustness of the results to the inclusion/exclusion set for speech recordings such that assessments made on:
Non-oral and VPI symptom recordings with less than 18 target words attempted are included;+Hypernasality recordings with less than 5 target words attempted are included;Audio recordings, where video recording not possible, for non-oral and VPI symptom are excluded;Any recordings taken outside of the speech recording follow-up window (Table 5) are excluded.

A multilevel logistic regression model (for insufficient VPC sum) adjusting for operating surgeon, size of cleft at baseline (soft palate only vs. soft and hard palate), randomised group, and an intercept will be applied to check the robustness of the results to an unadjusted analysis approach [21–24].

An exploratory analysis will be undertaken where the primary endpoint of insufficient velopharyngeal function, defined as a score of 4–6 on VPC sum, also includes patients who have a secondary surgery due to velopharyngeal insufficiency. This group will be compared to patients who have a score of 0 to 3 on the VPC sum scale and have not received a secondary surgery due to velophyngeal insufficiency. This redefined binary endpoint will be compared using a chi-squared test, with the relative risk [20] and 95% CI also reported.

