## Methods and design

### Trial design

TOPS is an international, multi-centre trial using a parallel arm design aiming to detect whether surgery at 6 months is superior to surgery at 12 months. Infants with a diagnosis of cleft palate are randomised to receive primary surgery for cleft palate using a standardised technique (the Sommerlad technique [12]) at either 6 months or 12 months (corrected for gestational age). Eligible patients are randomised on a 1:1 basis using minimisation routine, incorporating a random element to reduce predictability, to balance the two groups by surgeon (*n* = 24) and size of cleft (soft palate only vs. soft and hard palate). The nature of the intervention prevented this trial from being blind to participants or their carers. However, speech outcomes, at ages 12 months, 3 years, and 5 years, will be rated blind to the randomly allocated group by independent assessment of speech recordings taken at visit. The primary outcome is assessed at age 5 years with secondary outcomes assessed 48 h and 30 days post-surgery and at age 12 months, 3 years, and 5 years. Full details of the trial design, study population, and study procedures have been published previously [1].

The trial is registered with the ClinicalTrials.gov Identifier: NCT00993551 (registered: 9 October 2009).

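### The primary test and all secondary analyses ignore the two minimisation factors, so they are conservative and lose some power if surgeon or cleft size predicts outcome

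*SAP article*

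**What the plan says.** Under Trial design the SAP article states: "Eligible patients are randomised on a 1:1 basis using minimisation routine". The routine has a random element and is meant "to balance the two groups by surgeon" (24 of them) and by whether the cleft involves the soft palate only or the hard palate as well.

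Under Analysis of primary outcome neither factor enters the main comparison: "The numbers of insufficient velopharyngeal function or not between the randomised groups will be compared using a chi-squared test". An unadjusted relative risk and its 95% interval accompany this test. The same section then plans "A multilevel logistic regression model (for insufficient VPC sum) adjusting for operating surgeon, size of cleft at baseline", with randomised group and an intercept. Its role is limited: it "will be applied to check the robustness of the results to an unadjusted analysis approach".

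For secondary outcomes, the subsections on dichotomous, short ordinal, and long ordinal and continuous outcomes specify crude tests (chi-squared, chi-squared for trend, t test or non-parametric equivalent). Each says that there will be no sensitivity analysis.

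**The concern.** Minimisation forces the arms to be alike on surgeon and cleft size. A chi-squared test computes its variance as if that balance had arisen by chance. Outcome variation between surgeons and cleft sizes is then counted as noise in the comparison, although the design has largely removed it. If the factors matter, the reported interval is too wide and the p value too large.

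The trial has little power to spare. Trial status reports 558 children recruited, against the 648 planned under Sample size. The trial chose these two factors for balancing and adjusts for both in its own check, so it already treats them as possibly prognostic.

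A smaller wording matter adds to this. Minimisation uses the surgeon and the model uses the operating surgeon. The article does not say whether these are always the same person.

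**Working it through.** **1. The plan's own figures.** Inputs from Sample size: 40% vs 29%, two-sided 0.05, 80% power, chi-squared test. With pooled variance and no continuity correction, the mean rate is 0.345 and

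n = [1.96 × √(2 × 0.345 × 0.655) + 0.8416 × √(0.40 × 0.60 + 0.29 × 0.71)]² / 0.11² = (1.3176 + 0.5620)² / 0.0121 = 292 per arm.

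This matches the plan. At 300 per arm the three stated powers (81%, 80%, 76%) come out as 81.1%, 80.9% and 76.3%. The sample size contains no arithmetic error.

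**2. Power at the achieved size.** 558 × 0.9 = 502, or 251 per arm. Then z = (0.11 × √251 − 1.3176) / 0.6678 = 0.637, so crude power for 40% vs 29% is 73.8%.

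**3. Why the crude test is conservative.** Suppose the two factors explain a share R² of the outcome variance and balance is perfect. The true variance of the arm difference is then about (1 − R²) times the one the crude test uses. Its real type I error is 2 × [1 − Φ(1.96 / √(1 − R²))]. With R² = 0 this is 5%. With R² = 0.25 it is 2 × [1 − Φ(2.263)] = 2.4%.

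**4. Size of the effect, by simulation.** The article gives no prognostic strength, so these are assumptions: surgeon SD from 0 to 1.0 on the logit scale (intraclass correlation 0 to 1.0 / (1.0 + 3.29) = 0.23) and cleft odds ratio from 1 to 4. Minimisation was run on 24 surgeons and cleft size with an assumed 0.8 biased coin. Marginal rates were held at 40% and 29%, because that is the effect for which the plan is powered.

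Crude test against an adjusted analysis with a random surgeon intercept and fixed cleft size (linear approximation), 502 analysed:

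| Assumed effects | Crude power | Adjusted power | Difference |
|---|---|---|---|
| none | 72.3% | 72.5% | 0.2 |
| moderate | 73.7% | 76.6% | 2.9 |
| strong | 75.5% | 82.3% | 6.8 |

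Crude type I error fell to 2.4%, against 5.1% for the adjusted analysis.

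Crude test against a Mantel-Haenszel test stratified into 48 surgeon-by-cleft cells, 502 analysed, 4000 trials per cell:

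| Surgeon SD, cleft OR | Crude power | Stratified power | Crude type I error |
|---|---|---|---|
| 0, 1 | 73.6% | 71.5% | 5.6% |
| 0.3, 1.5 | 73.4% | 72.3% | 5.1% |
| 0.5, 2 | 74.1% | 74.6% | 4.0% |
| 0.8, 3 | 74.6% | 77.7% | 3.6% |
| 1.0, 4 | 76.2% | 81.5% | 2.4% |

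The Monte Carlo standard error in the second table is about 0.3 points for type I error and 0.6 to 0.7 points for power. Stratifying into 48 cells costs 1 to 2 points when the factors are weak. The random-intercept analysis shows no such cost.

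**The case against.** The strongest defence is that the plan is coherent. The sample size was calculated for a chi-squared test and that test is primary. A model adjusting for both factors is pre-specified, so readers will see an adjusted result. The crude test errs only towards caution. All of this stands, and it makes the point a recommended improvement and not a fatal fault. It is also true that the benefit is nil if the factors carry no prognostic information, and that a finely stratified test could lose a little. That small loss, however, belongs to the 48-cell test and not to the planned multilevel model.

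Four stronger readings are tempting, and the document does not support them.

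- **The robustness model adjusts for a variable affected by the arm.** The operating surgeon is settled at surgery, after randomisation and later in one arm. But nothing in the article shows that this person differs from the minimisation surgeon for any child, or changes more often in the 12-month arm.
- **An odds ratio cannot check a relative risk.** At the design rates the relative risk is 0.29 / 0.40 = 0.725 and the odds ratio is (0.29 / 0.71) / (0.40 / 0.60) = 0.61, so the two numbers should not be set side by side. Direction and significance can still be compared, so the check is not invalid.
- **Crude power collapses as surgeon effects grow.** This appears if the conditional odds ratio is fixed at 0.61, because the marginal difference then shrinks. With 40% and 29% held, crude power does not fall.
- **False positives are inflated.** The calculations show the opposite.

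**Conclusion.** The point holds as a conditional loss of efficiency. The primary test, relative risk and interval, and every secondary comparison, leave out the factors on which allocation was minimised. If surgeon or cleft size predicts outcome, the crude results are conservative. Over the assumed range, the adjusted analysis gains about 0 to 7 power points on a crude power of about 72 to 75%, and crude type I error drops from about 5% to about 2.4%. These sizes rest on assumed prognostic strength, an assumed biased coin of 0.8, 10% attrition from 558 and a linear approximation to the logistic model. The direction does not depend on the exact values. The ambiguity over the operating surgeon needs clarifying but is not a demonstrated bias.

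**What to change.** Before the outcome data are analysed by arm:

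1. Make the already planned multilevel logistic model the primary analysis, with randomised arm, baseline cleft size and a random intercept for the surgeon used in the minimisation.
2. From it, report a standardised (marginal) relative risk and risk difference with 95% confidence intervals, so that the headline measure stays on the planned scale.
3. Name a fallback for non-convergence, for example a Mantel-Haenszel relative risk.
4. Keep the crude chi-squared test and relative risk as supportive.
5. Replace the operating surgeon with the surgeon recorded at randomisation, as a safeguard.
6. Apply the same adjustment to the secondary outcomes where event numbers allow.

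The cost is a change of SAP wording and slightly more programming, with a possible convergence problem that the fallback covers. The sample size section can stand: with no prognostic effect, the adjusted analysis had practically the same power as the crude test.
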